### Study design

The trial component of the *CoV-Surv Study* is designed as a two-factorial, randomized, controlled, multi-arm, prospective, interventional, single-blinded trial with cluster sampling and four study arms, each representing a different SARS-CoV-2 testing and surveillance strategy. Figure 1 outlines the schedule of enrolment, interventions, and assessments.

**Fig. 1 Fig1:**
[figure not shown]
Schedule of enrolment, interventions, and assessments

#### Strategy A1

Individuals (one per household) receive information and study material by mail with instructions on how to produce a saliva sample and how to return the sample by mail. Once received by the laboratory, the sample is tested for SARS-CoV-2 using RT-LAMP.

#### Strategy A2

Individuals (one per household) receive information and study material by mail with instructions on how to produce their own as well as saliva samples from each household member and how to return these samples by mail. Once received by the laboratory, the samples are tested for SARS-CoV-2 using RT-LAMP.

#### Strategy B1

Individuals (one per household) receive information by mail on how to complete a brief pre-screening questionnaire which asks about COVID-19-related clinical symptoms and risk exposures. Only individuals whose pre-screening score crosses a defined threshold will then receive additional study material by mail with instructions on how to produce a saliva sample and how to return the sample by mail. Once received by the laboratory, the saliva sample is tested for SARS-CoV-2 using RT-LAMP.

#### Strategy B2

Individuals (one per household) receive information by mail on how to complete a brief pre-screening questionnaire which asks about COVID-19-related clinical symptoms. Only individuals whose pre-screening score crosses a defined threshold will then receive additional study material by mail with instructions on how to produce their own as well as saliva samples from each household member and how to return these samples by mail. Once received by the laboratory, the samples are tested for SARS-CoV-2 using RT-LAMP.

Of the four surveillance strategies, strategy A1 is considered the gold standard for prevalence estimation and thus used to determine the bias introduced by each of the other strategies. To determine the cost-effectiveness, each strategy is compared to a status quo, defined as the currently practiced passive surveillance approach. In each strategy, RT-LAMP-positive samples are additionally analyzed with real-time quantitative RT-PCR (RT-qPCR) in order to minimize the number of false positives.

### Study setting

The *CoV-Surv Study* is conducted in the city of Heidelberg and the neighboring Rhein-Neckar district located in the Southwest of Germany. The combined catchment area includes approximately 700,000 inhabitants. During the first pandemic wave in May 2020, the 4-week cumulative SARS-CoV-2 prevalence of symptomatic cases for the study population was about 0.25%.

### Characteristics of participants

Eligible are individuals age 7 years or older living in the Rhein-Neckar District or Heidelberg who consented (by a legal guardian in case of minors) to provide a self-collected saliva sample (all study strategies) after completion of a brief questionnaire (strategies B1 and B2 only). For the qualitative component complementing the trial, different samples of trial participants and non-participants (i.e., eligible persons who refused to participate) are identified for an additional interview. For these interviews, only individuals age 18 years or older are eligible.

### Study materials

Participants are asked to provide a saliva sample in a testing tube after gargling with 5ml saline solution. This sample is shipped to the laboratory by mail and then analyzed for SARS-CoV-2 using the RT-LAMP test. All positive-tested samples undergo additional confirmation analysis using the RT-PCR test. Depending on the strategy, some participants first take part in an online pre-screening survey. This short survey contains between 10 and 15 questions assessing the presence of symptoms of an early SARS-CoV-2 infection. This survey also collects information on a participant’s socio-demographic background (i.e., education, employment, household size). Participants of the qualitative study component further take part in a qualitative survey or an interview with open-ended questions. Participation in this qualitative study will commence after an individual’s trial participation has been completed.

To estimate the cost of the four surveillance strategies, an activity-based micro-costing approach is used to prospectively estimate the average cost per case completely screened and per case detected for each strategy. Data on the resource consumption of all activities related to the implementation of the four strategies will be categorized as either start-up or implementation cost. For each activity, data on resource consumption for both capital cost items (e.g., building, equipment, and vehicles) and recurrent cost items (e.g., personnel, materials, and consumables) will be collected directly from respective trial records. Unit costs will be taken from secondary data sources, such as financial statements, invoices, and salary schedules.

### Study-related processes

Participants assigned to strategy A1 are initially contacted by postal mail and receive an information letter outlining and describing the study purpose, the study procedure, the consent processes, and a declaration of consent. This initial letter also contains contact information of the study-specific hotline provided with the support of the local health department. The materials for self-sampling (including a testing tube with a unique barcode identification number) together with a stamped return envelope and instructions on how to return the sample as well as the consent form are also provided in this initial letter. The information letter further contains a link to an online video that provides instructions for the self-sampling procedure. In strategy A1 completion of a short SARS-CoV-2 symptoms survey also provided to each participant is voluntary.

Participants assigned to strategy A2 receive in addition to the above testing materials for up to three of their household members and instructions on how to order additional testing materials via the hotline if necessary. The cover letter also includes additional information on the declaration of consent for each participating household member. Completion of the SARS-CoV-2 symptoms survey is voluntary for each household member.

Participants assigned to strategy B1 are initially contacted by postal mail and receive an information letter outlining and describing the study purpose, the study procedure, the consent processes, and a declaration of consent. This initial letter also contains contact information of the study-specific hotline provided with the support of the local health department. Prior to receiving testing materials, these participants are asked to consent to and complete an online (smartphone, tablet, and computer-compatible) SARS-CoV-2 symptom pre-screening survey (to be completed by a legal guardian in case of minors). A paper-based back-up option for pre-screening is provided to participants without online access. Only participants with a positive result based on the pre-screening will receive testing materials by postal mail.

Participants assigned to strategy B2 are in addition to the above asked to conduct the initial pre-screening with all of their household members and will then receive testing material for those individuals in the household with a positive screening result.

All tested participants are able to query their test results online using the unique identification number assigned to them. In cases with a positive RT-LAMP test, participants are further informed about the additional RT-qPCR confirmation test. Once this test confirms a SARS-CoV-2 infection, the local health department is informed about the case and the participant will be directly contacted by the health department for additional routine contact tracing.

Participants of the qualitative component are contacted either by mail or phone and receive an information letter outlining and describing the purpose of this quality study component and related consent processes.

### Randomization process

The total study sample consists of 10,000 participants with each strategy enrolling 2500 randomly selected participants. Participants are identified and sampled by each selected municipality’s population register provided by the respective registration office. Individuals or households are drawn as a stratified sample proportional to population size. For each of two strata (i.e., all municipalities located in the “Rhein-Neckar District” or in the municipality of the city of “Heidelberg”), individuals or households are drawn in three batches of each three continuous weeks.

For the “Rhein-Neckar District” stratum, a two-stage sample design is used for each batch, within which the primary sampling units (PSU) are drawn as synthetic clusters of secondary sampling units (SSU) (i.e., individuals or households). First, 55 PSUs are randomly selected for each batch independently using probability proportional to size sampling. These 55 PSUs are then distributed across the 56 municipalities (i.e., sampling points) in the “Rhein-Neckar District” stratum using the Cox algorithm. This might result in some sampling points to contain several PSUs. Second, disproportional sampling is used to draw the same number of SSUs for each sampled PSU in order to obtain a self-weighted sample of individuals or households [19]. Since sampling points can contain several PSUs, the number of SSUs per sampling point and batch may vary. As the “Heidelberg” stratum consists only of one municipality, selection of individuals or households is carried out in a single-step simple random sampling process.

The net sample size is then translated into a corresponding gross sample under consideration of the expected response rates in each strategy and the sensitivity and specificity of the pre-screening tool applied to strategies B1 and B2 (see below). The gross sample therefore includes a total of 21,739 individuals or households contacted in the “Rhein-Neckar District” and 6386 in the “Heidelberg” stratum. This way a sample of 28,125 individuals or households is drawn and then randomly allocated to the four strategies A1, A2, B1, and B2 in the ratio 5 to 2.5 to 14 to 7 to eventually yield a final study sample of 2500 saliva tests for each strategy.

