### Power calculation

Based on a dynamic Bayesian prevalence estimate, the successful surveillance strategy is expected to test up to 1000 saliva samples per day in order to generate 2- to 5-week predictions on critical care capacity and other relevant health care parameters in the Rhein-Neckar [22]. Each studied strategy should therefore be able to estimate SARS-CoV-2 prevalence with sufficient accuracy. In May 2020, the 4-week cumulative SARS-CoV-2 prevalence estimated by passive monitoring in the Rhein-Neckar District was around 0.25%. Assuming an equally high prevalence of asymptomatic SARS-CoV-2 carriers, the overall prevalence of asymptomatic and symptomatic carriers was approximately 0.5%. A similar prevalence is assumed for future waves.

Strategy A1 is designed to directly reflect the pandemic events using a purely random sample. With a total of 2500 saliva samples, this strategy is able to detect an overall SARS-CoV-2 prevalence of 0.5% with an accuracy of ±0.35% and a power of 95%; a prevalence of 0.2% would be detected with an accuracy of ±0.25% and a power of 93% (confidence interval according to Agresti-Coull) [23]. Assuming a higher SARS-CoV-2 prevalence within families or households of an infected individual, strategy A2 is expected to detect this higher rate accordingly. Given the upstream pre-screening mechanisms and resulting filter effects in strategies B1 and B2, the resulting detection rates related to these strategies should also differ accordingly.

Sample sizes are therefore designed to yield 2500 saliva samples available for analysis in each study arm. The catchment area of the study (i.e., Rhein-Neckar District plus Heidelberg) has approximately 700,000 inhabitants. To ensure sufficient precision of the measured estimates, a total net case number of 1.4% of the target population (i.e., 0.35% per study arm) is targeted. Based on assumptions on participation rates as well as the sensitivity and specificity of the pre-screening tool, the following gross sample sizes are needed for each strategy:

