For strategy A1, a response rate of 50% is assumed after one-time prompting, warranting a gross sample of at least 5000 addresses per batch; for strategy A2, an average household size of two with a response rate of 50% after prompting is assumed, warranting a gross sample of at least 2500 addresses per batch [24]. For strategy B1, a 50% response to the first letter and a 50% response to prompting is assumed; further, a response rate of 80% is assumed for those participating in the pre-screening with positive screening results. To ensure a total of 2500 tested samples, at least 3125 test kits must be mailed out for this strategy. Assuming the pre-screening tool’s sensitivity at 90% and specificity at 70% and given a SARS-CoV-2 prevalence of 0.5%, at least 10,313 (=3125/0.303) participants have to complete the pre-screening. Further assuming a 50% response to the initial pre-screening tool and a 50% response after prompting warrants a gross sample of at least 13,750 addresses. Similar to above, for strategy B2 an average household size of two members is assumed, which warrants a gross sample of at least 6875 addresses. For the entire trial, a minimum gross sample of 28,125 addresses is required.

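### The allocation ratio 5 : 2.5 : 14 : 7 is a rounded form of the planned gross samples; applied to 28,125 addresses it leaves A1 and A2 1.3% below their stated minima

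*Protocol article*

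**What the plan says.** The Randomization process section of the protocol article fixes the total ("This way a sample of 28,125 individuals or households is drawn") and then gives the rule by which it is "randomly allocated to the four strategies A1, A2, B1, and B2 in the ratio 5 to 2.5 to 14 to 7", with the stated purpose "to eventually yield a final study sample of 2500 saliva tests for each strategy".

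The Power calculation section derives the gross sample of each arm from the assumed response rates, household size and pre-screening accuracy:
- A1: "warranting a gross sample of at least 5000 addresses per batch"
- A2: "warranting a gross sample of at least 2500 addresses per batch"
- B1: "warrants a gross sample of at least 13,750 addresses"
- B2: "which warrants a gross sample of at least 6875 addresses"

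It closes with a trial minimum of 28,125. For A1 alone it states a precision. Given 2500 saliva samples, "this strategy is able to detect an overall SARS-CoV-2 prevalence of 0.5% with an accuracy of ±0.35% and a power of 95" per cent, using the Agresti-Coull interval. A second scenario has 0.2% prevalence, ±0.25% and 93%.

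**The concern.** The four minima use up the whole total, so there is no slack. A ratio that gives any arm more than its minimum must take addresses from another arm. The printed ratio is larger in the two B positions than the minima imply, so the addresses come from A1 and A2.

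A1 is the arm that matters most here. The protocol treats it as the reference for prevalence, against which the bias of the other strategies is measured, and it is the only arm with a stated precision. Precision of the detection rate is also a primary outcome. The ratio is written as the operative allocation rule, and the number contacted in each arm is the denominator of the participation rate, so the text should give one consistent set of arm sizes.

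**Working it through.** **Inputs (all from Power calculation unless noted).** A1 response 50%. A2 household size 2, response 50%. B arms: 50% answer the pre-screening at once and 50% of the rest after prompting, so 0.5 + 0.5 × 0.5 = 0.75; kit return 80%; sensitivity 90%, specificity 70%, prevalence 0.5%; household size 2 in B2. Total 28,125 and the ratio come from Randomization process.

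**1. Reproducing the minima.**
- A1: 2500/0.5 = 5000. A2: 2500/(2 × 0.5) = 2500.
- Screen-positive share: 0.005 × 0.9 + 0.995 × 0.3 = 0.303.
- B1: 2500/0.8 = 3125 kits; 3125/0.303/0.75 = 13,751 (stated 13,750). B2: 13,750/2 = 6875.
- Sum: 5000 + 2500 + 13,750 + 6875 = 28,125, as stated.

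**2. Applying the printed ratio.** 5 + 2.5 + 14 + 7 = 28.5. Arm size = 28,125 × entry/28.5.

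| Arm | Stated minimum | From ratio | Difference | Expected samples |
|---|---|---|---|---|
| A1 | 5000 | 4934 | −66 (−1.3%) | 4934 × 0.5 = 2467 |
| A2 | 2500 | 2467 | −33 (−1.3%) | 2467 × 2 × 0.5 = 2467 |
| B1 | 13,750 | 13,816 | +66 (+0.5%) | 13,816 × 0.75 × 0.303 × 0.8 = 2512 |
| B2 | 6875 | 6908 | +33 (+0.5%) | 6908 × 2 × 0.75 × 0.303 × 0.8 = 2512 |

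**3. Reproducing the A1 precision.** Take the Agresti-Coull half-width as z·√(p̃(1 − p̃)/ñ), with ñ = n + z², p̃ = (x + z²/2)/ñ and z = 1.96. The 95% level is an assumption, since the article does not state it. Read the power as the binomial probability that the half-width is within the limit.
- n = 2500, prevalence 0.5%, limit 0.35%: 18 positives give 0.348%, so P(X ≤ 18) = 94.9% (stated 95%).
- n = 2500, prevalence 0.2%, limit 0.25%: P(X ≤ 8) = 93.2% (stated 93%).

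Both stated figures reproduce.

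**4. Effect of the smaller A1.** The number of A1 samples is random. At 50% response its standard deviation is √(5000 × 0.25) ≈ 35. Averaging the probability in step 3 over that distribution:
- 0.5% prevalence: 94.0% from 5000 addresses, 93.0% from 4934.
- 0.2% prevalence: 92.4% from 5000 addresses, 91.1% from 4934.

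The chance of reaching at least 2500 A1 samples is about 51% from 5000 addresses and about 18% from 4934.

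**5. Check of the corrected ratio.** 5 : 2.5 : 13.75 : 6.875 = 8 : 4 : 22 : 11, which sums to 45. 28,125/45 = 625, giving 5000, 2500, 13,750 and 6875 exactly.

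**The case against.** The strongest reply is that the ratio is shorthand. The exact arm sizes are printed in the Power calculation section, the Randomization section points forward to it, and the gap is within the uncertainty of the inputs. An A1 response of 2500/4934 = 50.7% instead of 50% would remove the deficit, and 33 samples is less than one standard deviation of the A1 count. All of this stands as an argument about size. It does not remove the contradiction: the total, the four minima and the ratio cannot all hold, and nothing in the text marks the ratio as approximate.

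A reader might go further and infer that A1 misses its 95% power and that about 92% should be stated instead. The documents do not support that, for three reasons.
- The 95% is stated for 2500 samples, and for that number it is right. The allocation ratio does not falsify it.
- Putting n = 2467 into step 3 with a limit of exactly 0.3500% does give 92.4%, because 18 positives then give 0.353%. That is a step caused by the discrete count: the figure is 92.0% at n = 2485 and 95.1% at n = 2486. If the half-width is read to the two decimals the protocol prints, n = 2467 gives 95.4%.
- In the 0.2% scenario, fixing n at 2467 gives 93.6%, above the 93.2% at n = 2500. A figure that moves in opposite directions in the two scenarios is not a measure of lost precision. The averages in step 4 are, and they show a loss of about 1 point (1.0 at 0.5% prevalence, 1.4 at 0.2%).

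**Conclusion.** The inconsistency is certain and minor. The printed ratio takes 66 addresses from A1 and 33 from A2 and gives them to arms that already meet their minima. Expected yield in each A arm is then about 2467, not the intended 2500, and the average A1 assurance at 0.5% prevalence drops by about 1 point.

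This rests on the following:
- The minima are whole-trial figures. The A1 and A2 sentences say per batch, and the sampling uses three batches, but tripling only those two gives 3 × 5000 + 3 × 2500 + 13,750 + 6875 = 43,125, and tripling all four gives 84,375. Only the whole-trial reading yields 28,125.
- The ratio was applied literally to that total. The article does not show whether it was.
- The protocol's own response rates hold, A1 responses are independent, and the interval is at the 95% level.

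That 13.75 and 6.875 were rounded to 14 and 7 with the total left unchanged is the likely explanation, but the article does not say so.

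**What to change.** In Randomization process, state the ratio as 8 : 4 : 22 : 11 (equal to 5 : 2.5 : 13.75 : 6.875). This returns all four stated minima from 28,125 addresses and costs one corrected line.

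Recruitment finished on December 22, 2020, so the allocation itself can no longer be changed, and the sponsor should say which ratio was used. If it was the rounded one, report the gross size achieved in each arm and note that A1 and A2 were expected to yield about 2467 samples each. Leave the 95% as a statement about 2500 samples, and do not replace it with 92%. Keeping 5 : 2.5 : 14 : 7 and still meeting every minimum would have needed 28,500 addresses, 375 more than planned.

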### Additional study samples

For the qualitative component, up to 60 in-depth interviews will be conducted with up to 30 study participants (up to 15 in each of the A and B arms) and with up to 30 participation refusers (up to 15 in each of the A and B arms). Both samples are purposefully selected from the quantitative trial sample to ensure all genders and age groups are represented. These samples serve to explore experiences and perceptions of being subjected to health surveillance and study participation. Further, up to 25 asymptomatic SARS-CoV-2-positive study participants are purposefully selected to explore how asymptomatic men and women diagnosed with SARS-CoV-2 give meaning to their diagnosis and to the dialectic between “feeling healthy” while simultaneously having a high likelihood of transmitting the virus to others. In addition, 100 randomly selected trial participants will be sampled to explore study participants’ perspectives on the implementation of each strategy’s screening and testing processes.

### Statistical analyses

The primary analysis will consist of an intent-to-treat (ITT) evaluation. Secondary analysis will include an estimation of the complier average causal effect using standard instrumental variables [20]. Here, the instrumental variable represents the initial random ITT assignment to the four strategies. The effects on continuous primary and secondary endpoints (e.g., cost per fully screened person, cost per confirmed positive case, cost per asymptomatic case, precision of prevalence) are measured using standard ordinary least square regression. For the effects on binary endpoints, we will use the modified Poisson model [21]. Effects on ordinal categorical endpoints (e.g., participant satisfaction measured on a Likert scale) are measured using an ordered logistic regression. All analyses will be adjusted for clustering of standard errors at the level of the randomization unit (i.e., municipalities). Primary analyses will not account for any baseline covariates; secondary analyses will account for the baseline covariates of age and sex.

In order to comprehensively identify the most cost-effective surveillance strategy, the aforementioned ITT analysis is complemented by a cost-effectiveness analysis evaluating the cost-effectiveness of the four surveillance strategies in relation to the status quo of having only passive surveillance. The cost-effectiveness analysis and underlying micro-costing study adopt a health system perspective to account for all costs incurred at the level of the health system, including the economic costs of all resources consumed in relation to the implementation and maintenance of the four active surveillance strategies, as well as the cost of the comparator (i.e., the passive surveillance system). All costs are measured as continuous variables for each individual. To determine the cost-effectiveness of each of the four surveillance strategies, costs and effects (measured as the number of cases detected) will be set into relation to those of the status quo. Incremental cost-effectiveness ratios (ICERs) are computed for each surveillance strategy in relation to the status quo. The strategy with the lowest ICER is considered as most cost-effective and will then be further appraised in conjunction with information on the prognostic models (described below) to orient decision making on the choice of the most suitable surveillance strategy to be implemented in routine practice.

Prognostic models are based on current SARS-CoV-2-related hospitalization numbers and the test results derived from each strategy using a SEIHR (susceptible, exposed, infectious, hospitalized, removed) differential equation. While some parameters for this model are taken directly from the literature, others (e.g., base reproduction number, hospitalization rate) are modeled using a Bayesian approach. Given the rather simplified representation of the SARS-CoV-2 infection process in this model, the predictions will only include data within a defined time window to allow models to react more flexibly to changes in the course of the disease. The inference models are adapted to each strategy. Simulations predict each strategy’s ability to determine the time period in which a new outbreak can be detected with an acceptable probability.

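### The planned instrumental-variable complier effect does not identify the effect of receiving strategy B rather than A among people who would take part

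*Protocol article*

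**What the plan says.** The Protocol article, Statistical analyses, makes intent-to-treat the primary analysis and adds: "Secondary analysis will include an estimation of the complier average causal effect using standard instrumental variables". It names the instrument: "Here, the instrumental variable represents the initial random ITT assignment to the four strategies".

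The other relevant facts are spread over several sections:

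- Randomization process: all sampled addresses are "randomly allocated to the four strategies A1, A2, B1, and B2 in the ratio 5 to 2.5 to 14 to 7". There is no fifth arm.
- Strategy B2: passive surveillance is a comparator for cost-effectiveness ("To determine the cost-effectiveness, each strategy is compared to a status quo, defined as the currently practiced passive surveillance approach"), not a randomised arm. In the same place, "strategy A1 is considered the gold standard for prevalence estimation and thus used to determine the bias introduced by each of the other strategies".
- Study-related processes: A1 and A2 addressees get sampling kits with the first letter. In B1 and B2 a kit is sent only after a positive pre-screen, so someone who does not complete the pre-screen gets no kit.
- Power calculation: "For strategy A1, a response rate of 50% is assumed after one-time prompting"; for A2, "an average household size of two with a response rate of 50% after prompting is assumed". For B1, half respond to the first letter and half to prompting, and 80% of those who screen positive return a sample. B2 is derived from B1 by household size alone.

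**The concern.** Standard instrumental variables recover a complier effect when assignment acts on the outcome only through the treatment received, and when that treatment is the contrast of interest. Here a person who does not respond receives no strategy at all, and this is expected for half of the A addressees and a quarter of the B addressees. Strategy received therefore has five states (none, A1, A2, B1, B2), while assignment supplies four arm means.

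For B versus A there are two difficulties. The people who take part under B need not be those who take part under A. And someone who would return a sample under A1 but would not complete the pre-screen goes untested under B1. For that person assignment changes the outcome although B was never received, so the exclusion restriction fails.

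At stake is a secondary result carrying a causal label in a trial meant to choose the strategy for routine use. If its sign can depend on how treatment received is coded, it could mislead that choice.

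**Working it through.** **Inputs** (Protocol article, Power calculation): response 50% in A1 and A2; average household size 2; pre-screen response 50%, then 50% of the rest; kit return 80%; pre-screen sensitivity 90%, specificity 70%; prevalence 0.5%. Further assumptions for this check: the outcome is a detected case per contacted index person, an untested person counts as not detected, every tested infection is detected, and responders have the 0.5% prevalence.

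**1. Reproduce the plan's gross sample.**
- Pre-screen positive: 0.005 × 0.9 + 0.995 × 0.3 = 0.303
- Kits: 2500 / 0.8 = 3125; completers: 3125 / 0.303 = 10,313.5 (plan: 10,313)
- Pre-screen response: 0.5 + 0.5 × 0.5 = 0.75
- B1: 10,313.5 / 0.75 = 13,751 (plan: 13,750); B2: half, 6,876 (plan: 6,875)
- A1: 2500 / 0.5 = 5000; A2: 2500 / (2 × 0.5) = 2500
- Total: 28,127 (plan: 28,125)

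The figures agree up to rounding, so 50% against 75% is the plan's own assumption.

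**2. Intent-to-treat difference, B1 minus A1.**
- A1: 0.50 × 0.5% = 0.25%
- B1: 0.75 × 0.5% × 0.9 × 0.8 = 0.27%
- Difference: +0.02 points

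**3. Wald estimates.** The share tested is 0.50 in A1 and 0.75 × 0.303 × 0.8 = 0.182 in B1.

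| Treatment received, D | First stage, B1 minus A1 | Wald estimate (points) |
|---|---|---|
| received B1 | 0.75 - 0 = 0.75 | 0.02 / 0.75 = +0.03 |
| responded | 0.75 - 0.50 = 0.25 | 0.02 / 0.25 = +0.08 |
| tested | 0.182 - 0.50 = -0.318 | 0.02 / (-0.318) = -0.06 |

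Taken literally, the last row says that being tested lowers the chance of detection. It arises because B1 tests fewer, pre-selected people.

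**4. The contrast for people who would take part in both.** Under A1 they are detected at 0.50%. Under B1 they are detected at 0.5% × 0.9 × 0.8 = 0.36%. The difference is -0.14 points if detection is homogeneous among responders. No coding in step 3 gives this value, and two give the opposite sign.

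**5. What the data could say about it.** Suppose every A1 responder would also complete the B1 pre-screen. A1 responders are then 0.50 / 0.75 = 2/3 of B1 completers, whose overall detection is 0.36%.
- Upper limit: all B1 detections fall in that two-thirds, 0.36% / (2/3) = 0.54%; contrast 0.54 - 0.50 = +0.04 points.
- Lower limit: all fall in the other third, 0%; contrast 0 - 0.50 = -0.50 points.

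**6. A2 versus A1.** With D = responded, the first stage is 0.50 - 0.50 = 0. With D = household testing and A1 as control, the effect is identified if the same people respond in both arms. Assuming 0.5% prevalence in the second member, A2 yields 0.50 × (0.5% + 0.5%) = 0.50% per address. Then (0.50 - 0.25) / 0.5 = 0.50 points of extra cases per complying household.

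**The case against.** The strongest reply is that the Wald ratio does estimate something well defined. With A1 responders nested in B1 completers, two-thirds of completers would take part in both (effect -0.14) and one-third only under B1 (effect +0.36, since under A1 they go untested). The average is 2/3 × (-0.14) + 1/3 × 0.36 = +0.03 points, exactly the ratio for D = received B1. Raising participation is part of what a strategy does, and the participation rate is a secondary outcome. This stands: under nesting that ratio validly estimates the effect of being assigned B1 rather than A1 among B1 responders. But it is a different quantity from the effect of strategy on people who take part in both. It needs nesting, which the article does not state, and it fails if some people respond only under A.

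A second reply is that treatment received, complier and reference are normally defined in an analysis plan, which is not shown. Their absence is indeed no finding. However, the estimator, instrument, arms and kit rules are fixed here. Defining terms would not supply the missing cross-arm response assumption, and adding that assumption or bounds goes beyond standard instrumental variables.

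Third, a reader might infer that the lack of an untreated arm alone defeats the method. It does not. If non-compliance were only crossover to A1, four unknowns would face four arm means. Some crossover is real: an A2 addressee who tests alone has in effect received A1. Setting undetected to zero for the untested also makes the system solvable, but each ratio is then just the detection rate among that arm's own responders.

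**Conclusion.** The point holds for A-versus-B contrasts. As specified, the complier analysis does not point-identify the effect of receiving B rather than A among people who would take part. On the plan's rates the estimate for B1 minus A1 is +0.03, +0.08 or -0.06 points by coding, against -0.14 points in the stratum that would take part in both. That last figure rests on responders sharing the 0.5% prevalence and on homogeneous pre-screen sensitivity and kit return. The bounds of -0.50 to +0.04 points rest on nesting.

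Two stronger readings are not supported. One is that the analysis would show only a difference in response: for A versus B the estimate also carries the 0.9 × 0.8 pre-screen and return losses, and for A2 versus A1 the assumed response is equal. The other is that no complier effect can be estimated in this trial: household uptake in A2 versus A1 can be, under the same-responders assumption. The analysis is secondary, and the primary intent-to-treat comparison is unaffected.

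**What to change.** For A-versus-B contrasts, replace the standard instrumental-variable estimate with one of two things: bounds for the stratum that would take part under either strategy, or a principal-stratum estimate whose cross-arm response assumption (nesting, for example) is stated and varied. Label any per-participant comparison between A and B as non-randomised. Keep instrumental variables only for household uptake in A2 versus A1, with household testing as the treatment received, A1 as control and the same-responders assumption written down.

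The cost is modest extra analysis and wording, and the loss of a point-identified causal label for A versus B. Design, sample size and primary analysis do not change.
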